Logistic regression models will be used with GDM as binary response variable and predictor as explanatory variable. Predictor-effects will be presented as odds ratios with 95% confidence intervals and p-values will be reported. Besides univariable analyses, a multivariable prediction model will be built, ultimately leading to a risk score definition for predicting the risk for developing GDM. A backward selection procedure will be applied for model building. A complete case analysis is planned, implying that all observations are used in the analysis for which all model variables are observed. In case of substantial missing data in predictor variables leading to power loss in the multivariable analysis, the technique of multiple imputation for dealing with missing data will be applied.

##### To analyze for aim 4

The economic evaluation will establish the cost-utility of the one-step IADPSG screening strategy from the health care payer perspective. To calculate QALYs, utility values of relevant health states (such as perfect health, GDM, preterm birth, permanent brachial plexus injury) are derived from the literature and combined with the time spent in the health state. Clinical data (such as the risk of preterm birth, the risk of GDM) are derived from the BEDIP-N study. Cost data are collected by the centers participating in the BEDIP-N study and are also extracted from the literature. The cost-utility is calculated as the cost per QALY gained in the base case analysis. A probabilistic sensitivity analysis is conducted to explore the robustness of cost-utility results to values of input parameters. Results of the probabilistic sensitivity analysis are presented on the cost-effectiveness plane and in a cost-effectiveness acceptability curve.

A 5% significance level will be adopted for all tests and all tests will be 2-sided. All analyses will be performed using SAS software, version 9.3 of the SAS System for Windows.

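### The GDM risk score comes from backward selection on complete cases, with imputation triggered only by power loss: unless the full plan corrects this, weak predictors are overstated and predicted risks may be biased

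*Protocol article*

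**What the plan says.** In the protocol article, under Power calculation and statistical analyses (To analyze aim 2), logistic models with GDM as the outcome are fitted one predictor at a time and also jointly: "a multivariable prediction model will be built, ultimately leading to a risk score definition for predicting the risk for developing GDM". The method is stated: "A backward selection procedure will be applied for model building". The output named is "Predictor-effects will be presented as odds ratios with 95% confidence intervals and p-values will be reported".

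On missing data the default is "A complete case analysis is planned, implying that all observations are used in the analysis for which all model variables are observed". The exception reads "In case of substantial missing data in predictor variables leading to power loss in the multivariable analysis", in which case "the technique of multiple imputation for dealing with missing data will be applied". A general rule closes the section: "A 5% significance level will be adopted for all tests and all tests will be 2-sided".

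The sections Evaluation of insulin sensitivity and beta-cell function and Measurement of lipids and inflammatory biomarkers add that HbA1c, insulin, lipids, vitamin D, adiponectin, leptin and Hs-CRP are assayed in all women with diabetes or GDM but only in a control group or subgroup of the others.

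**The concern.** Three stated choices interact.

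- **Selection.** When predictors are kept because they look strong in the data, the kept coefficients are too large on average, most of all for weak predictors. A score built from them gives risks that are too extreme, and its performance in the same data looks better than it will in new women.
- **Imputation trigger.** The plan treats missing predictors as a loss of precision. Whether complete-case analysis is valid depends on why values are missing, not on how much power is lost.
- **Outcome-dependent assays.** If the subgroup biomarkers become predictors, having a complete record depends on having GDM.

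Aim 2 is meant to yield a simple screening algorithm, and the Discussion expects public health impact from it. Such an algorithm depends on predicted risks that hold in new women.

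**Working it through.** **Inputs from the article:** N = 2563; 5% excluded for overt diabetes; 12.4% of the remainder with GDM. **Not given, so assumed below:** number of candidates, stay criterion, predictor strength and correlation, amount of missing data, size of the control subgroup.

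**1. The plan's own figure.** 2563 is sized for a chi-square comparison of macrosomia between GDM and non-GDM, not for a prediction model. With k = 0.876/0.124 = 7.06 non-GDM women per case, two-sided 5%, 80% power and pooled variance, the total is n(GDM) × (1 + k)/0.95. The two macrosomia rates are cited but not stated, so 2563 can be neither reproduced nor refuted. Rates of 8% v 13.1% give 2555, and 16% v 22.65% give 2564. Nothing below depends on this.

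**2. Expected events.** 2563 × 0.95 = 2435 women; 2435 × 0.124 = 302 events. Events per candidate: 302/20 = 15.1; 302/40 = 7.5; 302/60 = 5.0.

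**3. Effect of selection.** Simulated logistic data: eight real predictors (log odds ratios per SD 0.5, 0.35, 0.25, 0.2, 0.15, 0.1, 0.1, 0.08), the rest noise, pairwise correlation 0.1, prevalence 12.4%. Backward Wald elimination at p < 0.05; 100 replicates; evaluation in 60,000 new subjects. Weak ratio = estimated/true log odds ratio for the four weakest real predictors when retained; strong ratio = the same for the two strongest. Differences were taken before rounding.

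| Women (events) | Candidates | Effects | AUC apparent / new | Difference | Slope | Weak ratio | Strong ratio |
|---|---|---|---|---|---|---|---|
| 2435 (302) | 10 | ×1 | 0.726 / 0.716 | 0.010 | 0.94 | 1.72 | 1.03 |
| 2435 (302) | 20 | ×1 | 0.728 / 0.715 | 0.012 | 0.94 | 1.64 | 1.01 |
| 2435 (302) | 40 | ×1 | 0.729 / 0.713 | 0.016 | 0.92 | 1.68 | 1.01 |
| 2435 (302) | 60 | ×1 | 0.732 / 0.703 | 0.029 | 0.86 | 1.58 | 1.02 |
| 1218 (151) | 20 | ×1 | 0.733 / 0.707 | 0.026 | 0.87 | 2.27 | 1.07 |
| 1218 (151) | 40 | ×1 | 0.740 / 0.698 | 0.041 | 0.80 | 2.29 | 1.09 |
| 2435 (302) | 40 | ×0.6 | 0.654 / 0.625 | 0.030 | 0.80 | 2.38 | 1.06 |
| 1218 (151) | 40 | ×0.6 | 0.667 / 0.611 | 0.056 | 0.66 | 3.60 | 1.20 |

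With 302 events and full effects, the noise variables kept average 0.8, 1.7 and 2.8 for 20, 40 and 60 candidates. To illustrate the weak ratio: a true log odds ratio of 0.10 (odds ratio 1.11) times 1.65 is 0.165, reported as 1.18. Each scenario uses one set of new subjects, so AUC differences should be read to about two decimals.

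**4. Sensitivity to the assumed effects.** With six independent predictors of log odds ratio 0.25 each (40 to 60 replicates), full data give AUC 0.67 apparent v 0.65 new and slope 0.88 for 20 candidates, and 0.68 v 0.65 and slope 0.84 for 40. The direction is the same and the bias somewhat larger.

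**5. The imputation trigger.** In a correctly specified logistic model, missingness that depends only on the predictors leaves the slopes valid; missingness that depends on both predictors and outcome biases them. A trigger that looks only at power cannot tell these apart.

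**6. Outcome-dependent assays.** Non-GDM women: 2435 − 302 = 2133. If controls are a random subgroup, complete-case slopes survive but the intercept shifts by ln(2133/number of controls).

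- One control per case: ln(2133/302) = 1.95. The event fraction becomes 50%, so a woman with true risk 12.4% is assigned about 50%.
- Two per case: ln(2133/604) = 1.26. The event fraction becomes 33%, and the same woman is assigned about 33%.

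If controls are not chosen at random, the slopes can be affected too.

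**The case against.** The strongest reply is that this is a short paragraph in a condensed article. Internal validation, shrinkage, the stay rule, the candidate list and performance measures normally sit in the analysis plan, which is not shown. That stands: the article's silence does not show that no optimism correction is planned.

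Several stronger readings are tempting, and the text does not support them:

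- **P-value selection at 5%.** No criterion is named; this can only be inferred from the general rule on tests.
- **Univariable screening of candidates.** The univariable analyses are set beside the multivariable model and are not said to feed it.
- **An inflated reported AUC.** No discrimination measure is planned in the article, only odds ratios.
- **All odds ratios too favourable.** Univariable ones are not selected, and strong predictors are inflated only 1.01 to 1.03 times with full data and full effects.
- **A large candidate set.** Aim 2 speaks of the most relevant factors and a simple algorithm. Collecting a variable does not make it a candidate.
- **A biased cost-effectiveness result.** The aim 4 text does not mention the score. The Discussion refers to a risk-factor approach without linking it to this model.

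It is also fair that complete-case analysis does not itself create optimism; it adds to it by reducing events. An imputation fallback is stated, and the large gaps in the biomarkers might trigger it. If it does, and the outcome is in the imputation model, the event fraction could be restored, but the article does not say so.

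What remains is stated text: backward selection, complete case as default, and a trigger tied to power.

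**Conclusion.** The point holds in a limited form. As written, the procedure gives over-large coefficients for weak retained predictors. Any apparent performance would be modestly optimistic unless the full plan corrects it: about 0.01 to 0.02 in AUC and a slope of 0.92 to 0.94 for 20 to 40 candidates at the main assumed effects. It becomes material with around 60 candidates, weaker predictors or loss of half the cases (slope 0.66 to 0.87 in the scenarios tabulated). Candidate number, effect sizes, correlation, the 5% stay rule and the case loss are assumptions.

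The imputation trigger is too narrow whatever those assumptions. The biomarker problem is conditional: it arises only if the subgroup markers enter the model on complete cases, but the distortion of predicted risks could then be large.

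A reader might infer that the published score will be uncorrected and its discrimination overstated. The article does not establish that.

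**What to change.** - **Selection.** Name the candidates and the stay criterion. Backward selection can stay, but repeat the whole process within bootstrap samples, report optimism-corrected discrimination and calibration slope, and shrink the coefficients before deriving the score.
- **Sporadically missing predictors.** Make multiple imputation primary, with the outcome in the imputation model, and keep complete case as a sensitivity analysis. Drop the power-loss trigger.
- **Subgroup biomarkers.** Weight by the control sampling fraction or correct the intercept, or leave these markers out of the score.

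If the analysis plan already contains these steps, a cross-reference is enough. The cost is more computing, some added analysis text and slightly less favourable reported performance. No new data are needed, provided the control sampling fraction is recorded.

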### Objective and aims of the Belgian Diabetes in Pregnancy Study (BEDIP-N)

Since many uncertainties remain concerning the on-step IADPSG screening strategy for GDM, a large prospective multi-centric cohort study was designed. The overall objective of the Belgian Diabetes in Pregnancy Study (BEDIP-N) is to evaluate the impact of the IADPSG screening strategy on the prevalence of GDM and pregnancy outcomes in an ethnic diverse population.

Specific aims are:

➢ Aim 1: To evaluate the use of a GCT as an universal screening tool in a two-step approach with the use of the 75 g 2-hour OGTT with the IADPSG criteria only if the GCT is abnormal.

➢ Aim 2: By using a multivariable risk estimation model based on the most relevant clinical risk factors and biochemical measures for GDM, the aim is to develop a simple screening algorithm.

➢ Aim 3: To evaluate differences in GDM prevalence and pregnancy outcomes using different diagnostic criteria based on the 75 g OGTT: the IADPSG criteria, the Carpenter & Coustan criteria and threshold values if diagnostic criteria would be based on an odds ratio of 2.0.

➢ Aim 4: To explore the cost effectiveness of the one-step IADPSG screening strategy.

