### Study sample

#### Study cohort

The cohort is recruited from 6 centers: UZ Leuven, the University hospital of Antwerp (UZA), Imelda hospital Bonheiden, OLV hospital Aalst-site Aalst, OLV hospital Aalst-site Asse and St Jan hospital Brussels. Five centers are situated in the Northern part of Belgium: 2 centers in the province of Flemish-Brabant, 1 center in East-Flanders and 2 centers in Antwerp. One center is situated in Brussels, the capital city of Belgium. There is a good mix between centers with an average number of women from an ethnic minority background (BME) and centers with a high percentage of women from a BME background (St Jan Hospital Brussels and OLV hospital Aalst-site Asse). UZ Leuven and St Jan Hospital Brussels have a mean number of deliveries of 2200 per year and the other centers have between 700–1000 deliveries per year.

The aim is to enroll 2563 pregnant women in the first trimester over a 2 year recruitment period (see next paragraph for power calculation). The minimum recruitment planned per center is around 175 women per year (depending on the center between 100–300 women per year) with a max. of 25% of the pregnant population that has to be recruited. Recruitment began in April 2014 and will end around October 2016.

The expected duration of the study depends on the results of the screening tests during pregnancy. If a diagnosis is made of overt diabetes in early pregnancy or if no GDM is diagnosed early or later in pregnancy, the study will end when women and the baby leave the hospital after the delivery. For these women, the max. duration of the study will be 8 months. If women are diagnosed with GDM (early or later in pregnancy), an extra visit is planned three months after the delivery. For these women the expected duration of the trial will be max. 11 months.

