#### Power calculation and statistical analyses

We aim at demonstrating a higher proportion of macrosomia (birth weight >4 Kg) in women with GDM compared to women without GDM based on the IADPSG criteria. We assume that 5% of recruited women develop overt diabetes in early pregnancy and will be excluded from the analysis. We assume that 12.4% of eligible patients will develop GDM using IADPSG criteria (value as reported in ATLANTIC-DIP study) [28]. The prevalences of macrosomia for GDM and non-GDM cases used in the calculations are also based on results reported in the ATLANTIC-DIP study [28]. We calculate that the total number of subjects needed to demonstrate a difference in proportions of pregnancy complications with 80% power and 5% significance level, is 2563. The sample size calculation is based on a two-sided Chi-square test.

##### To analyze the overall objective and aim 3

The proportion of GDM cases with 95% confidence intervals will be estimated for both 2-step and one-step screening strategies. The difference in proportions between both screening strategies will be tested using McNemar’s test for paired proportions. McNemar’s test will be used for testing differences in proportions between Carpenter & Coustan criteria and IADPSG criteria, and between IADPSG criteria and diagnostic criteria based on an odds ratio of 2.0. All analyses will be performed using all valid measurements. The chi-square test for proportions will be used for the comparison of GDM and non-GDM patients on binary or categorical variables. The Mann–Whitney U test will be used in case both groups are being compared on ordinal or continuous variables. A complete case analysis will be performed including all cases for which both GDM status and characteristic or complication are observed.

##### To analyze aim 1

Sensitivity, specificity, positive predictive value and negative predictive value will be determined for the 50 g GCT as a predictor of the result of the two-step 75 g 2-hour OGTT. The analysis will be performed using all cases with valid measurements on both tests.

##### To analyze aim 2

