### Outcomes of the study

#### The diagnosis of GDM

Diabetes and GDM in early pregnancy are resp. defined as diabetes and prediabetes outside pregnancy [23]. The diagnosis of GDM between 24–28 weeks of pregnancy is based on the IADPSG criteria [9]. For women with a diagnosis of diabetes or GDM, data on the treatment and glycemic control will be collected at each visit with the diabetes nurse, dietician and/or diabetologist. The following data are collected: whether glycaemic targets are met or not, when and why insulin is started and changes in the dose of insulin. All concomitant medication and/or supplements will also be recorded.

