### Other study measurements

#### Evaluation of insulin sensitivity and beta-cell function during pregnancy and postpartum based on the OGTT

At the three visits blood samples are taken to later determine HbA1c and insulin (fasting and at the different time frames of the 75 g OGTT). These analyses will be performed in all women with diabetes or GDM and in a control group of women without diabetes or GDM. Analyses will be performed at the central lab of UZ Leuven. HbA1c is measured by reversed-phase cation-exchange chromatography (ADAMS HA-8160, Menarini Diagnostics Benelux, Zaventem, Belgium). Plasma glucose is measured by an automated colorimetric-enzymatic method (hexokinase-glucose-6-phosphate-dehydrogenase, application 668) on a Hitachi/Roche-Modular P analyzer. Insulin is measured by the immunometric ECLIA (Roche Modular E170, Basel, Switserland).

Glycaemia will be assessed by the area under the glucose curve during the OGTT, calculated using the trapezoidal rule. Insulin sensitivity will be measured using the insulin sensitivity index of Matsuda and DeFronzo [37]. Beta-cell function will be assessed by the insulinogenic index dived by HOMA-IR [38]. The insulinogenic index will be calculated as the incremental change in insulin concentration during the first 30 min of the OGTT divided by the incremental change in glucose during the same period [39,40]. As a measure of beta-cell compensation, the insulin secretion sensitivity index (ISSI-2) will be measured [41,42]. All these measures are validated for use in pregnancy.

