#### Measurement of lipids and inflammatory biomarkers

Based on blood samples taken at visit 1, lipids (total cholesterol, HDL, triglycerides, calculated LDL), 25-OH vitamin D and the inflammatory biomarkers adiponectin, leptin and Hs-CRP will be measured at the Lab of Experimental Endocrinology of KU Leuven in the group with diabetes/GDM and in a subgroup of women without diabetes or GDM. Lipids will also be measured at visit 2 and visit 3. Lipids are measured by the immunoassay analyzer Cobas 8000 (Roche). Hs-CRP, leptin and adiponectin will be measured by the immunoassay system of Meso Scale Discovery, Gaithersburg, USA (coefficients of variability are < 10% for CRP, < 8.4% for leptin and <6.5% for adiponectin). 25 OH vitamin D will be measured by the competitive radioimmunoassay (DiaSorin, Stillwater, Minnesota, USA) as previously described [43].

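### Aim 2 fits the GDM risk score on complete cases, but several biochemical markers are assayed by outcome; if any is a candidate predictor, absolute risks come out too high

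*Protocol article*

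**What the plan says.** In the list of aims, aim 2 is a "multivariable risk estimation model based on the most relevant clinical risk factors and biochemical measures for GDM", leading to a simple screening algorithm. The paragraph on analysing aim 2, under Power calculation and statistical analyses, specifies logistic regression with GDM as the response, backward selection, and a final risk score. Its rule for missing values is: "A complete case analysis is planned, implying that all observations are used in the analysis for which all model variables are observed". The next sentence allows multiple imputation if missing predictor values are substantial and cost power.

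Two later sections fix who is assayed:

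- HbA1c and insulin (Evaluation of insulin sensitivity and beta-cell function): "These analyses will be performed in all women with diabetes or GDM and in a control group of women without diabetes or GDM".
- Lipids, 25-OH vitamin D, adiponectin, leptin and Hs-CRP at visit 1 (Measurement of lipids and inflammatory biomarkers): "in the group with diabetes/GDM and in a subgroup of women without diabetes or GDM".

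The article gives no size or selection rule for the control group, and no weighting or intercept correction for aim 2. Other measures do not have this restriction. Fasting plasma glucose (FPG) is measured in all women in the first trimester, the 50 g GCT is given to all who reach the 24–28 week screen, and the thyroid section states no limit to a subgroup.

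On the response, The diagnosis of GDM says: "Diabetes and GDM in early pregnancy are resp. defined as diabetes and prediabetes outside pregnancy". The aim 2 paragraph says only GDM, without stating whether early GDM counts.

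**The concern.** Whether a woman has an HbA1c, insulin, lipid or adipokine value depends on whether she has GDM. A complete-case model containing one of these markers keeps essentially all GDM women and discards non-GDM women because of their outcome. The cohort then becomes, in effect, a case-control sample. Logistic regression on such a sample estimates slopes properly under random control selection, but its intercept reflects the sampling ratio and not the population risk. Backward selection starts from all candidates, so one such marker restricts the sample used for selection even if it is later eliminated.

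The product is meant to state a woman's risk of GDM and to support a screening algorithm. If OGTT referral were tied to an absolute risk, a threshold read from the uncorrected score would not mean what it says.

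A smaller question concerns the response. Early GDM is defined by a visit-1 FPG of 100–125 mg/dl. If those women counted as events, visit-1 FPG would partly predict its own definition.

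**Working it through.** **The plan's own figure.** The article gives no number for aim 2. Its only sample-size figure, 2563, concerns macrosomia and cannot be recomputed, because the macrosomia rates used are not printed. Here it serves only as an input.

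**Inputs**

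- Enrolment (Study cohort): "The aim is to enroll 2563 pregnant women in the first trimester over a 2 year recruitment period".
- Exclusion (Power calculation): "We assume that 5% of recruited women develop overt diabetes in early pregnancy and will be excluded from the analysis".
- GDM prevalence (same section): "We assume that 12.4% of eligible patients will develop GDM using IADPSG criteria".
- Controls per GDM case, k: not stated. I assume 1 to 5, with full assay of all women as the no-bias limit.

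**Step 1, expected numbers.** 2563 × 0.95 = 2435 women. 2435 × 0.124 = 302 with GDM, leaving 2133 without. The ratio is 0.876/0.124 = 7.06 and does not depend on the 5% exclusion.

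**Step 2, effect of the sampling.** Let f = k × 302/2133 be the fraction of non-GDM women assayed. With all GDM women assayed and controls drawn at random, the complete-case model estimates logit(risk) − ln(f). All odds are multiplied by 1/f and the slopes are unchanged. The GDM share in the sample is 1/(1 + k).

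| k | f | GDM share | Odds multiplied by | Intercept shift | True 5% scored as | True 12.4% scored as | True 25% scored as | Non-GDM dropped |
|---|---|---|---|---|---|---|---|---|
| 1 | 0.142 | 50% | 7.06 | 1.955 | 27.1% | 50% | 70.2% | 86% |
| 2 | 0.283 | 33.3% | 3.53 | 1.262 | 15.7% | 33.3% | 54.1% | 72% |
| 3 | 0.425 | 25% | 2.35 | 0.856 | 11.0% | 25% | 44.0% | 58% |
| 4 | 0.566 | 20% | 1.77 | 0.569 | 8.5% | 20% | 37.1% | 43% |
| 5 | 0.708 | 16.7% | 1.41 | 0.346 | 6.9% | 16.7% | 32.0% | 29% |
| all | 1 | 12.4% | 1 | 0 | 5% | 12.4% | 25% | 0% |

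Example for k = 1: the odds at 5% are 0.05/0.95 = 0.0526; × 7.06 = 0.372; 0.372/1.372 = 27.1%.

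**Step 3, simulation.** I used 2435 women, two correlated predictors with true slopes 0.5 and 0.6, and 300 repeats. Mean predicted risk from the uncorrected complete-case fit, applied to the whole cohort, was 43.8% at k = 1 and 30.1% at k = 2 (both against 11.7% observed), and 19.0% at k = 4 (against 11.6%). Slopes at k = 1 were 0.51 and 0.59, against 0.50 and 0.60 in the full cohort. Adding ln(f) to the fitted intercept brought the mean predicted risk back to the observed prevalence.

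**Step 4, does the imputation trigger track the bias?** As an approximation for small effects, the precision of a log odds ratio relative to the full cohort is (1 + 1/7.06)/(1 + 1/k) = 1.142/(1 + 1/k). This gives 57%, 76%, 86%, 91% and 95% for k = 1 to 5. At 4 or 5 controls per case little precision is lost, yet the odds are still inflated 1.77-fold or 1.41-fold. A trigger based on power can therefore stay silent while the intercept is wrong.

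**The case against.** The article never lists the aim 2 candidates. It asks for the most relevant measures in a simple algorithm, places the subgroup-assayed markers under other study measurements, and in the Discussion presents the insulin and beta-cell work as pathophysiology. A score from clinical factors, FPG and GCT would not have this bias. This stands, and it makes the point conditional. It does not remove it: aim 2 names biochemical measures without limiting them to universal ones.

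The imputation fallback might well be reached, since at 1 to 3 controls per case more than half of the non-GDM women would lack these markers. With random controls and GDM status in the imputation model, it would restore the intercept. This also stands in part, but the trigger is power, and step 4 shows that power and bias need not move together.

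A reader might go further in four ways that the document does not support:

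- That predicted risks are certain to be far too high. The size depends on an unstated control ratio, and there is no bias of this kind if no subgroup-assayed marker is a candidate.
- That the score would necessarily send the wrong women to the OGTT. With random controls, ranking, sensitivity and specificity are preserved, so a cut-off chosen on those selects the same women. Only an absolute-risk threshold is distorted. Predictive values are planned for aim 1, whose tests are given universally, not for aim 2.
- That FPG is circular in the model. The text leaves the response ambiguous, and its wording about developing GDM, with the 24–28 week screen restricted to women without early GDM, points rather the other way.
- That the lack of an optimism correction is a defect. That is ordinary analysis-plan content, and nothing in the article excludes it.

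**Conclusion.** The point holds in conditional form. The complete-case rule for aim 2 conflicts with an assay plan that selects on outcome. If any of the listed markers is a candidate, the intercept, the absolute risks and any absolute-risk cut-off are biased upwards whenever fewer than all non-GDM women are assayed. Under the plan's 12.4% prevalence and an assumed 1 to 5 controls per case, the odds are inflated 7.06-fold down to 1.41-fold, and 86% down to 29% of non-GDM women are discarded. The direction is certain for a random subgroup; the size is not, because the ratio is not given. Odds ratios and discrimination are sound only if controls are chosen at random, which is also not stated. The definition of the response needs clarifying but is not a demonstrated error.

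**What to change.** For any aim 2 model that considers a subgroup-assayed marker, replace the unweighted complete-case rule. Draw the controls at random, record the sampling fraction f, and specify one of the following:

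- (a) weights of 1/f for the sampled non-GDM women and 1 for the GDM women;
- (b) ln(f) added to the fitted intercept, or equivalently a model offset of −ln(f) that is left out when predicting. The sign matters: an offset of +ln(f) doubles the error;
- (c) multiple imputation of the unassayed women with GDM status in the imputation model, required by the sampling design and not triggered by power loss.

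Otherwise, restrict the score to universally measured predictors: clinical factors, FPG and GCT.

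State also that the response is GDM on the 24–28 week OGTT among women without early GDM, so that visit-1 FPG does not predict its own definition.

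No extra women or assays are needed. The cost is wording, a little more analysis work, and somewhat wider intervals under weighting.
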